# An integrated approach to health, wellbeing, and productivity at work: a design of a stepped wedge worksite intervention study

**DOI:** 10.1186/s12889-023-16014-x

**Published:** 2023-06-02

**Keywords:** Occupational health and safety, Health promotion, Workplace health, Worker safety, Denmark, Musculoskeletal disorders, Mental health and wellbeing, Participatory approach, Organizational integration

## Abstract

**Background:**

Despite an intensive focus on workers’ health during recent decades, the prevalence of work-related diseases remains unchanged in Denmark and internationally. Therefore, USA and Australian researchers have initiated new paradigms for integration of health promotion, prevention of work-related disease, and organization of work. Inspired by the Australian WorkHealth Improvement Network program (WIN), this paper describes the background, design, intervention methodologies, and evaluation methods of an Integrated Approach to Health, Wellbeing, and Productivity at Work (ITASPA) intervention aiming to prevent work-related injuries and diseases and promote the health, safety, and wellbeing of the worker.

**Methods:**

Using a stepped wedge design, worksites will be enrolled at baseline and offered the intervention starting at different times. Data will be collected at baseline, before the off-set of the intervention, and after each implementation period. The effect evaluation will be based on a mixed-methods approach. The qualitative data are based on semi-structured interviews and focus groups. The quantitative data consists of questionnaires, anthropometrics, and resting blood pressure and will be analyzed based on the intention-to-treat principle in linear mixed models with random slope and intercept.

**Discussion:**

Integrated interventions are shown to increase overall health and safety at worksites more effectively and rapidly than more narrowly focused programs. Still, previous integrated interventions are lacking successful implementation. In ITASPA, the effects of the intervention is tested in a strong scientific mixed-methods design. Thus, the ITASPA project contributes to the knowledge about what characterizes a best practice for the implementation of integrated worksite interventions.

**Trial registration:**

ITASPA is retrospectively registered in Clinicaltrials.gov on May 19, 2023 (NCT05866978).

## Background

Despite the past decades’ increased focus on workers’ health, the Danish, as well as international prevalence of work-related diseases and injuries, remain stable [1, 2]. In Denmark, the most prevalent work-related diseases are musculoskeletal (MSDs) and mental disorders, e.g. work-related stress, depression, and anxiety [3], and the prevalence of work-related stress is increasing [4]. Such work-related diseases have negative consequences for the individual’s well-being and functional abilities and is a public health issue of major concern. Previously, worksite prevention of these conditions has mostly used single-faceted approaches addressing either health promotion (such as improving the general health and reducing chronic disease of the individual) or prevention of work-related risk factors for injuries or disorders [5]. However, separating activities addressing these two conditions are evidenced to limit their overall effectiveness [6]. Moreover, previous worksite interventions have lacked organizational integration [6]. To address the constant burden of work-related diseases and injuries and thereby ensure the safety and health of workers, leading health organizations have recommended better integration of the traditionally separate work health efforts [7–11]. However, little is known about best practice prevention [12], and more effective approaches to address and implement initiatives aiming to reduce work-related MSDs and mental disorders are needed.

The American Total Worker Health (TWH) [13] and the Australian WorkHealth Improvement Network (WIN) program [14, 15] are two examples of conceptualized integrated approaches towards health promotion and prevention of disease in work health interventions. TWH was introduced by NIOSH in 2011 with the overall aim of combining health promotion and prevention of work-related injuries and health risks factors in all work health interventions. Furthermore, TWH was based on the assumption that all contextual and work-related conditions affect the employee’s health behavior. The WIN concept operationalized the TWH approach and introduced an extended focus on systematic data collection and evaluation. Moreover, the WIN concept involved a collaborative element of knowledge-exchange across participating worksites and included ongoing adjustments of initiatives to improve the work health efforts.

Compared to the American work health system, the Australian system is more similar to the Danish, and the systematic approach and data collection in the WIN concept are possible to operationalize and have documented beneficial effects [15]. Therefore, our intervention ‘Integrated Approach to Health, Wellbeing, and Productivity at Work’ (ITASPA) is based on the concepts of WIN.

The aim of the ITASPA project is to investigate the effect of the WIN program in a Danish context. The hypothesis is that an integrated approach will improve the health of employees in terms of fewer MSDs, improved psychosocial wellbeing and workability, and strengthened occupational safety culture. Furthermore, the ITASPA project aims to examine the degree of implementation of the initiated initiatives and identify barriers and facilitating factors for implementation. This contributes to the knowledge about what characterizes best practices for the implementation of integrated worksite interventions.

## Methods

### Study design

ITASPA is a worksite intervention, conducted in a stepped wedge design (Fig. 1) [16]. The stepped wedge design are assumed to increase the willingness to participate as it allows all workers to receive the intervention. The workers function as their own control and thereby, the stepped wedge design allows for an effect-evaluation, mimicking an RCT design.

**Fig. 1 Fig1:**
[figure not shown]
The stepped wedge design. All worksites are included at baseline. The black boxes illustrate periods where worksites will function as controls. The white boxes illustrate where worksites will function as intervention worksites and the grey boxes illustrate where the intervention is implemented and maintained

The study was approved by the Danish data protection agency (journal number REG-034–2021) and the Ethics Committee for the regional capital in Denmark (journal number SJ-927) and will be conducted in accordance with the Helsinki declaration. The first version of the Clinicaltrials.gov registration for ITASPA is registered on May 19, 2023 (NCT05866978).

### Recruitment

To increase the transferring of the WIN program to a broad variety of Danish worksites, both public and private worksites are aimed to be enrolled. The worksites will be enrolled on basis of their willingness to perform the ITASPA activities during paid worktime and participation in the scientific evaluation of the ITASPA project. Workers will be included in the scientific evaluation of the ITASPA project by the following criteria: aged 18 – 67 years old at baseline; employed at one of the enrolled worksites ≥ 20 h/week; not being pregnant; ability to understand and speak Danish or English; providing an informed signed consent prior to participation.

An information meeting at the worksites will be held before initiating the intervention. At the meeting, the background and aim of the ITASPA project are introduced. All workers will be invited to fill out a screening questionnaire in which they can choose to sign up for participation in the scientific evaluation.

### Power calculation

The sample size estimations were based on effect expectations in MSDs, on a scale ranging from 0–10, an expected variance of 2.1, an Alpha value of 0.05, and a power of 80%. The estimation showed a cluster size of 65 participants to identify a statistically significant effect, at a 5% level, of the worksite intervention.

### Development, planning, and preparation of the itaspa intervention

#### Organization of the project

The ITASPA project will be organized by a steering group consisting of the ITASPA project managers, representatives from the senior management at the enrolled worksites, and the ITASPA facilitators from the Department of Occupational and Social Medicine at Holbæk Hospital, Denmark (Fig. 2). Moreover, the steering group includes an advisory board consisting of the developers of the WIN program and TWH concept. The advisory board will provide information about international experiences with integrated worksite interventions to assist the development of worksite health interventions in Denmark.

**Fig. 2 Fig2:**
[figure not shown]
Flowchart of the organization of ITASPA

#### Development of ITASPA package of change

The steering group will collect and choose relevant tools and methodologies to establish a Package of Change. This package encompasses descriptions of the processes in ITASPA, evidenced examples of previous successful worksite interventions similar to ITASPA, and the present work environment policy, program, and practice at the enrolled worksites.

#### ITASPA committee at the worksite

At each worksite, an ITASPA committee will be established (Fig. 2). In accordance with an integrated approach, the members will represent the existing cooperative work environment fora, the workers, union and safety representatives, and relevant staff functions (HR, etc.). The worksites choose a chairperson for the ITASPA committee, who will be leading the interventions and act as the contact to the ITASPA facilitators. Ideally, the chairperson of the committee is a line manager who has knowledge of change management and communicates with both employees and senior management.

#### Education of the ITASPA committee

Before the offset of the intervention, the ITASPA committee will be educated by the ITASPA facilitators in the ITASPA concept and the Package of Change.

The education session will be carried out as a workshop (education workshop, Fig. 3) at the enrolled worksites during paid work time. The workshop lasts 3 h and involves training in collaborative methodology, the models of improvements (e.g. the model of Change), the plan-do-study-act (PDSA) cycle, and the integrated concept of worksite intervention used in ITASPA [17]. A central theme for the education workshop is the Model of Improvement which consists of two parts. The first brainstorming part includes three key questions aiming to guide the assessment of which initiatives each worksite should focus on: 1) What are we trying to accomplish?, 2) How will we know that a change is an improvement?, and 3) What changes can we make that will result in an improvement?) [17]. The second part is the “test part”, which consist of the PDSA cycles:• Plan: Thorough planning of the initiative, clarification of expectations of outcomes, and agreements on data collection.• Do: Implementation of the planned actions as well as data collection.• Study: Reflection on effect and learning, data analysis, and identification of unintended negative and positive consequences.• Act: Assessment of either continuation of implementation, adjustments, or testing a new initiative.

**Fig. 3 Fig3:**
[figure not shown]
Process of the ITASPA intervention

The experiences from each cycle will systematically be transferred to the next. Thus, continuous improvements and/or adjustments will be conducted.

#### Workshops for choosing, planning, studying, and evaluating initiatives

In workshops (learning workshops, Fig. 3), the ITASPA committees will develop their initiatives based on their own experiences of their work environment. Methods used in the Australian WIN study [17] will guide the ITASPA committee in this process. Finally, success criteria will be set, and the committee will decide what data should be used to evaluate the effect of the initiative. All decisions will be documented by the ITASPA facilitators.

#### ITASPA committee network

Following the first implementation period, the ITASPA committees from all participating worksites will be invited to join a network. In this network, the ITASPA committees learn from each other, share ideas and give each other feedback. Each ITASPA committee will describe their worksite initiatives, the preliminary intended and unintended effects, and the facilitating factors and barriers for testing and implementation of their initiatives. The network meetings will be facilitated by the project manager and an ITASPA facilitator, who will lead the discussion and give feedback.

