### Ethical considerations

The implementation of the project within worksites depends on the consent of the top management. At learning workshops, worksites will be encouraged to share experiences with their work environment initiatives. During this process, company-sensitive information may be shared. Thus, in workshops, it will be pointed out that a duty of confidentiality is expected among companies.

Personal information will be obtained from the participants about safety at work, workability, MSD, and psychosocial well-being. Data will be stored and processed as prescribed by the Danish Data Protection Agency and will only be available to researchers involved in this study. Data will be anonymized in analyses and feedback to the worksite will be provided anonymously, and in groups of at least 10 participants. The ITASPA facilitators will discuss any unforeseen ethical aspects with the worksites if they experience any. In this context, the steering group and reference group will be involved as potential sparring partners.

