### Strengths and limitations

Even though RCTs are the golden standard for intervention studies, it is not always practically possible, nor feasible, to have a control group of employees working at worksites that will not be affected by the intervention. However, the stepped wedged design will function as an RCT as it allows for comparison of control and intervention effects within the same environment, without increasing the risk of contamination between the intervention and control group, which reduces the risk of bias. Moreover, a stepped wedge design can prevent ethical objections arising from withholding an intervention anticipated to be beneficial [28]. In addition, a stepped wedge design will overcome issues with impaired organizational commitment and disappointed participants in the control group since all participants will be offered the intervention, and thus increases the participants’ obligations to the project [25]. Yet, the stepped wedge design still allows a sound scientific evaluation in a RCT design and address important ethical considerations, thereby increasing the possibility of a high number of participants and compliance, leading to stronger estimates in our data analysis.

Some limitations of the intervention design also deserve to be mentioned. As all employees will receive the intervention, it is not possible to blind participants or those involved in delivering the intervention. Hence, information bias may appear, particularly when outcomes are subjective. E.g. it is possible that participants are likely to report more positive health outcomes due to extended awareness of changes in these conditions after having received the intervention, leading to stronger effect-estimates of the intervention [28].

Furthermore, selection bias may challenge the generalizability of the results: it is plausible that healthy workers are more likely to stay at work longer than those who are injured or made sick from work [29] (healthy worker selection bias). This may reduce the potential to identify adverse health effects from work, leading to weaker estimates of the effect of risk factors on the health outcomes. However, by using a screening questionnaire we can examine if those who want to participate are different from those who do not want to participate.

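### The network invitation is not limited to worksites that have crossed over, which does not fit the claim that the design adds no contamination risk

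*Protocol article*

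**What the plan says.** The Methods part of the abstract states that "worksites will be enrolled at baseline and offered the intervention starting at different times". The caption of Fig. 1 adds: "The black boxes illustrate periods where worksites will function as controls". At any moment before the last step, some worksites are therefore active while others supply control data.

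The section ITASPA committee network sets the rule for contact between worksites. After the first implementation period, "the ITASPA committees from all participating worksites will be invited to join a network". In the network, committees learn from one another and report their initiatives, the early intended and unintended effects, and what helped or hindered them. An implementation period lasts about three months (Periods of implementation).

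The section Effect evaluation and analyses codes the intervention as a two-level fixed effect, control period against intervention period. Under Strengths and limitations, the article presents it as an advantage that the design allows this comparison "without increasing the risk of contamination between the intervention and control group". The limitations that follow cover lack of blinding, information bias and healthy-worker selection. Contamination is not among them.

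**The concern.** The effect estimate rests on the contrast between control and intervention periods, so it is only as good as the separation between the two. The network rule names all participating worksites and sets no condition that a worksite must have started. A facilitator who followed it literally could invite a waiting worksite about three months into the study.

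What would pass across is not incidental. The Background names exchange of knowledge across worksites as an element of the Australian WIN concept and says that ITASPA is based on WIN. A waiting worksite in the network would receive a component of what is being tested, together with other sites' ideas and early results.

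If that content helps, control periods improve, the contrast shrinks, and a null result could not be told apart from a diluted one. The bias runs toward no effect. It would not create a false positive.

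**Working it through.** **Setting the passages side by side**

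1. Abstract (Methods) and Fig. 1 caption: enrolment is simultaneous, starts are staggered, and waiting worksites are controls.
2. ITASPA committee network: the invitation follows the first implementation period and goes to committees of all participating worksites. The text does not say whether that period belongs to the study or to each worksite.
3. If it is the study's first period, worksites in later steps are still controls when they are invited. If it is each worksite's own, they are not.
4. Background: cross-worksite exchange is part of the programme concept. Under the first reading, part of the programme therefore enters control periods.
5. Strengths and limitations: no increase in contamination risk is claimed. This fits the second reading only.

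So the network section and the claimed strength agree only under a restriction that the article does not state.

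**Size**

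No figure in the document measures contamination. Power calculation gives a variance of 2.1, alpha 0.05, power 80% and a cluster size of 65. The 65 cannot be reproduced, because the article states no effect size, intracluster correlation or number of clusters. The illustration below does not need it.

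Assume a two-sided test at 0.05, and that control periods on average carry a share c of the full effect. The estimated effect is then multiplied by (1 − c). With 80% power at c = 0, the standardised effect is 1.9600 + 0.8416 = 2.8016, so

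- power = Φ[2.8016 × (1 − c) − 1.9600]
- sample-size factor to regain 80% = 1/(1 − c)²

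| c (assumed) | argument of Φ | power | sample-size factor |
|---|---|---|---|
| 0 | 0.842 | 80% | 1.00 |
| 0.10 | 2.5214 − 1.9600 = 0.561 | 71% | 1/0.81 = 1.23 |
| 0.20 | 2.2413 − 1.9600 = 0.281 | 61% | 1/0.64 = 1.56 |
| 0.30 | 1.9611 − 1.9600 = 0.001 | 50% | 1/0.49 = 2.04 |
| 0.50 | 1.4008 − 1.9600 = −0.559 | 29% | 1/0.25 = 4.00 |

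These figures hold for any test with 80% power and a diluted effect. They ignore clustering and the step layout. Control measurements taken before the network opens, baseline included, are untouched by it, so c is an average over exposed and unexposed control data and could be small or zero.

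**The case against.** The strongest reply is that the network is meant for worksites that have already started. Each committee is to describe its own initiatives and their early effects, and a waiting worksite has none. The section also sits in a description of the process each worksite goes through, which suggests that the first implementation period is the worksite's own. The article does not say when a waiting worksite's committee is formed, so there may be no committee to invite. The figures with the step layout and process are not shown, and detailed scheduling may sit in a fuller protocol. This stands as far as it goes: exposure of control worksites is not established. It does not settle the matter, because the sentence says all worksites and sets no condition.

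It can also be said that the contamination claim concerns treated and untreated colleagues in one workplace and not exchange between companies. That reading is possible. The sentence, however, speaks of intervention and control groups without qualification, and the limitations do not raise between-worksite contact.

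A reader might infer two further routes, and neither is supported:

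- **Learning workshops.** Ethical considerations says: "At learning workshops, worksites will be encouraged to share experiences with their work environment initiatives". But committees develop their own initiatives in these workshops, and a data collection is scheduled before the first one. A worksite in its own workshops therefore appears to have begun the intervention. The sentence introduces a confidentiality point and does not say that control worksites attend.
- **Steering group.** It includes "representatives from the senior management at the enrolled worksites", and "The steering group will collect and choose relevant tools and methodologies to establish a Package of Change". That places managers in the planning. Nothing says that their membership brings initiatives to workers during control periods, and the outcomes are measured in workers.

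**Conclusion.** The point holds as a gap in a stated rule that does not fit a stated claim. The network invitation lacks a crossover condition, and followed literally it could carry programme content into control periods and bias the only effect contrast toward no effect. The article claims no added contamination risk and lists no such limitation.

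It would be too strong to say that waiting worksites will be exposed. The article leaves open whose first period is meant, and its description of what committees report suits worksites that have started. It would also be too strong to quote a power loss for this trial. The 71%, 61% and 50% rest on an assumed average share of 10%, 20% and 30%, a two-sided test, and a simple calculation without clustering or steps. Only the direction follows from the design, and only if the shared content benefits those who receive it.

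**What to change.** 1. In ITASPA committee network, state that a worksite joins the network, and receives other worksites' preliminary results, only after its last control-period measurement and its own first implementation period. If that was always the intention, one clause is enough.
2. Record any earlier contact between worksites (who, when, and what was shared) as process data, so that its extent can be reported beside the effect estimate.
3. In Strengths and limitations, qualify the contamination statement and list between-worksite contamination as a limitation, with its expected direction.

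The cost is wording, a small addition to process tracking, and smaller network meetings early in the study, when few worksites qualify. The knowledge-exchange element of the programme is kept, and each worksite reaches it after crossing over. The steering group and the preparation of the Package of Change need no alteration for this purpose.
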